## Abstract

**Background:**

The quality of registry based studies depends largely on the data accuracy of the registries. The Dutch Perinatal Registry (Perined) is a nationwide database comprising perinatal data digitally provided by different healthcare providers. Perined data are used for comparing outcomes across regions and healthcare institutions as well as for quality analyses and research purposes. However, little is known about the data quality of the Perined database. Therefore, this research protocol depicts our proposed study assessing the quality of Perined data compared to hospital records and case report forms (CRFs) that were part of the IUGR Risk Selection (IRIS) study.

**Methods:**

In the planned comparison study data from Perined and the IRIS Study will be used. The IRIS study was a large cluster-randomized trial investigating the effectiveness of routine third trimester ultrasonography in reducing severe adverse perinatal outcomes among Dutch low-risk pregnant women. A subsample of the IRIS study of neonates being at risk of severe adverse perinatal outcomes and their mothers will be used. Baseline demographic data were collected by midwives from participating women at inclusion (around 22 weeks’ gestation) using CRFs, and in-depth neonatal and maternal clinical data were retrieved from hospital records by trained research assistants. These latter IRIS study data were linked and compared to Perined data. Completeness of Perined data will be calculated for every variable. The reliability will be assessed as the percent of agreement between Perined and hospital record data or the CRF-based data. Additionally, intra-class correlation coefficients will be calculated for continuous variables, and Kappa and ‘Prevalence-and-Bias-Adjusted Kappa’ will be calculated for categorical variables.

**Discussion:**

The results of the planned comparison study will provide users of Perined data insight in its data quality. This will serve as an example of the accuracy of registry based data used in maternal and neonatal care research.

## Introduction

Many countries have a nationwide perinatal database containing data on maternal and neonatal outcomes, such as mode of birth and birth weight.
^
1
^
^–^
^
3
^ Countries use national perinatal data for monitoring outcomes, quality analyses and research. The data can also be used for comparing results between hospitals, midwifery practices and regions within the country and between countries.
^
2
^
^,^
^
4
^
^–^
^
6
^ For example, EURO-PERISTAT merges aggregated data of all EU members states, Norway, Iceland, Switzerland and the United Kingdom for comparing maternal and neonatal outcomes between the countries.
^
2
^ For these purposes, high quality of the data included in these national databases is essential. Nevertheless, there is a lack of research and insufficient insight into the data quality of these databases.

In 2018, a study was published about the completeness of birth registries worldwide. Phillips et al. concluded that in 2011 only 40% of the total births in the world were registered in a public database, although registration was better in high income countries.
^
1
^ In 2019, two Canadian studies were published on the data accuracy of one of two of the Ontario Birth Registries: the BORN (Better Outcomes Registry and Network.
^
7
^
^,^
^
8
^ Miao et al. compared the BORN birth registry with the general Canadian clinical hospital database (n = 404,439) by evaluating data on key maternal and neonatal outcomes.
^
7
^ Dunn et al. compared data from BORN with data extracted from hospital records (n = 927), and focussed on key outcomes, e.g. labour type and gestational age at birth, but also considered more specific maternal and neonatal outcomes, e.g. ‘pain relief measures during newborn screening’ or ‘serum bilirubin’.
^
8
^ Both studies found an overall good agreement for most key maternal and neonatal outcomes, e.g. almost perfect agreement for gestational age at birth and date of birth.
^
7
^
^,^
^
8
^ Remarkably, in the study of Miao et al. the lowest Kappa was found for stillbirth or live birth (Kappa 0.74), because of discrepancies in the coding of stillbirths between the data sources.
^
7
^ The study by Dunn et al. using hospital records as comparison found lower agreement for more specific outcomes, e.g. intention to breastfeed and maternal smoking, than for key outcomes.
^
8
^ The BORN birth registry has also been compared to another Canadian birth registry: CIHI-DAD (Canadian Institute for Health Information Discharge Abstract Database).
^
9
^ When lower agreement between variables was found, disagreement could often be explained by differences in coding or differences in definitions of the compared variables.
^
9
^ Another study conducted in Finland in 2002 on the Finnish medical birth registry showed that check-box questions improved data quality, compared to open-ended questions.
^
10
^ In addition to research on the accuracy of birth registry databases, studies concerning the data quality of non-perinatal databases showed that the overall completeness, validity, and reliability of national medical databases in high income countries was good and has improved over the years.
^
11
^
^–^
^
15
^

The planned study focuses on the evaluation of the quality of data obtained from the Netherlands Perinatal Registry (Perined).
^
16
^ Such an evaluation is crucial as Perined serves important healthcare-related and scientific purposes. The aim of Perined is to improve the quality of Dutch perinatal care.
^
16
^ The database is used for comparing outcomes between regions, midwifery practices and hospitals, for quality analyses to improve perinatal care and research.
^
4
^ The database contains data on pregnancy, birth and neonatal outcomes.
^
4
^ The data are collected by midwives, obstetricians and paediatricians as part of their regular practice, and a selection of items is shared with Perined.
^
16
^ In 2020 97% of all Dutch births were registered in Perined.
^
4
^

Several large-scale Dutch studies used Perined data, for example the DELIVER (Data EersteLIjns VERloskunde) study, ABCD (Amsterdam Born Children and their Development) study and the IRIS (IUGR RIsk Selection) study.
^
17
^
^–^
^
19
^ These studies all had more than 5000 participants. Data in these studies were collected in different ways and Perined data were used for key maternal and neonatal outcomes. Other studies are completely based on Perined data, e.g. the development of the latest Dutch birthweight charts.
^
20
^

This illustrates that Perined data are regularly used for research purposes. However, to the best of our knowledge, the data quality of the Perined database has never been assessed in a study. Therefore, the aim of the planned study is to assess the data quality of the Perined database, by assessing the completeness and agreement of the data as compared to perinatal and maternal peripartum variables based on the original hospital records and baseline demographic data from the IUGR Risk Selection (IRIS) study.

## Methods

### Design

This research protocol depicts a data comparison study concerning a subsample of data based on the IRIS study.
^
19
^
^,^
^
21
^ To assess agreement, data from Perined will be compared with data extracted from hospital records from the participating mothers and/or neonates or with demographic baseline data collected via Case Report Forms (CRFs) at enrolment of participating women (around 22 weeks’ gestation) completed by the midwives together with the participants.
^
19
^
^,^
^
21
^ The data extracted from the hospital records and CRF-based demographics of the IRIS study are used as reference standards. In short, the IRIS study was a multi-centre nationwide stepped wedge cluster randomized trial investigating the effectiveness of routine ultrasound screening in the third trimester of pregnancy in reducing severe adverse perinatal outcomes in low risk pregnancies.
^
19
^ Routine third trimester ultrasound screening was compared with standard care. Sixty primary care midwifery practices in the Netherlands and a total of 13,520 women with a low risk singleton pregnancy participated in the IRIS study. The women were enrolled between February 2015 and February 2016. Data of 13,024 (96.3% of 13,520) participating mothers and neonates were linked to Perined data.
^
19
^ Data extracted from the hospital records (n=2884) were collected for neonates at risk for severe adverse perinatal outcomes and for mothers with an at risk neonate and/or with indications of peripartum pathology or hospitalization (see section
*data collection and selection* for more details and variable operationalization).

### Perined data

Data for this study were collected in 2015 and 2016. In 2016 98% of the Dutch births were registered in Perined.
^
22
^ Each profession registers a set of variables.
^
23
^ Perined links the datasets of each profession and creates one record for all neonates and their mothers (
Figure 1).
^
24
^ Some variables are uniquely registered by the respective healthcare providers of one profession, whereas others (e.g. type of birth) are registered by healthcare providers of multiple professions. For every variable that is registered by more than one profession, Perined uses a decision tree to determine which value is leading in the Perined record.
^
24
^ The records used in this study are all records with information from more than one healthcare profession, thus having a complex data structure. In 2015 and 2016 Perined started with a new registration approach for hospitals in the Netherlands. Some hospitals used the new approach, while others still used the old approach. The old and the new approach differ in the variables that are recorded, some variables have been added in the new approach (e.g. length and weight of the pregnant woman), while others have been removed (e.g. method of conception). Also, for some variables answer options have been changed. For the IRIS study, most of the data were provided according to the old approach. The data provided according to the new approach have been recoded by Perined according to the specifications of the old approach.

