## Conclusion and discussion

The planned study with data of the IRIS study provide a unique opportunity to validate the Perined dataset on a large scale. In recent years the Dutch Perined database has been increasingly used for various purposes, e.g. benchmarking between Dutch regions, benchmarking between nations, and various types of research. However, so far, little is known about the data quality of Perined despite its importance for healthcare evaluation and research purposes.

The planned study will have some strengths and limitations. The greatest strength of this study is that using a large-scale nationally representative low risk pregnancy population in the Netherlands provides the rare opportunity to validate the quality of Perined data. A potential limitation is that the data collection for the IRIS study was conducted in the years 2015 and 2016. These years were so-called ‘transition years’ for the Dutch perinatal registration during which Perined implemented a new dataset system. For the IRIS study the ‘old’ way of data registration and coding were used. Data from participating care institutions that already used the new approach were recoded to fit in the old dataset format as depicted above. A priori one might assume that this may have influenced the degree of missingness in some perinatal variables. The linkage rate between Perined and the complete IRIS study data was very high (96.3%) as compared to a recent study with a much lower linkage rate (78.5%) using the ‘new data registration approach’ only.
^
19
^
^,^
^
33
^ Data used for this study were mostly based on complex records reported by different healthcare professionals, see
Figure 1. In several instances, information on a certain variable, e.g. birth weight, was entered by several healthcare professionals so that a decision rule was used by Perined determining from which healthcare profession data should be used for a specific variable. One might assume that the accuracy of variables registered by only one healthcare profession may be more accurate than for those variables entered by multiple professions. However, this is unavoidable as for a large group of women and their offspring in ante- and postnatal care referred from midwifery-led care to obstetrician-led care data is generally entered into the Perined database by multiple healthcare professions.
^
4
^

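### Agreement on CRF-referenced demographics appears confined to the at-risk subsample of 2,884, although up to 13,024 linked women could supply it, and the text conflicts on which records are analysed

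*Protocol article*

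**What the plan says.** **Reference data.** The Design section treats the extracted hospital records and the CRF demographics as reference standards. On the CRFs, the abstract states: "Baseline demographic data were collected by midwives from participating women at inclusion (around 22 weeks’ gestation) using CRFs". They were therefore completed before it was known which pregnancies would later meet the at-risk criteria.

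**Numbers.** The Design section reports that "a total of 13,520 women with a low risk singleton pregnancy participated in the IRIS study" and that "Data of 13,024 (96.3% of 13,520) participating mothers and neonates were linked to Perined data". Of the hospital data it says: "Data extracted from the hospital records (n=2884) were collected for neonates at risk for severe adverse perinatal outcomes", and it adds mothers with an at-risk neonate or with signs of peripartum pathology or hospitalization.

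**Sample.** The abstract says: "A subsample of the IRIS study of neonates being at risk of severe adverse perinatal outcomes and their mothers will be used". The section on Perined data says: "The records used in this study are all records with information from more than one healthcare profession, thus having a complex data structure". The Discussion says instead: "Data used for this study were mostly based on complex records reported by different healthcare professionals". The section on data collection and selection describes the comparison as one between the selected hospital records and CRFs and the Perined records of the same people. The section on statistical analyses, however, allows the completeness denominator to be either the hospital-record dataset or a CRF-based dataset, and gives no size for the latter.

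**Discussion.** It suggests that variables registered by one profession may be more accurate than variables entered by several. On the women referred to an obstetrician, whose data several professions generally enter, its next sentence begins: "However, this is unavoidable as for a large group of women and their offspring in ante- and postnatal care referred from midwifery-led care". It also names as the study's greatest strength a large, nationally representative low-risk population.

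**The concern.** A variable that is checked against the hospital record can be assessed only where a record was extracted. A variable that is checked against the CRF has no such limit. If both kinds are nevertheless assessed in the same at-risk subsample, the CRF results describe records that were selected on outcome: perinatal death, low Apgar score, low birth weight with or without a neonatal stay, or maternal or neonatal care reported in the survey. All or most of these records were assembled from more than one profession's entries.

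Readers would use the completeness and agreement figures for demographics as figures for Perined in low-risk pregnancies generally, because the Discussion presents the sample in those terms. A subsample chosen for pathology does not support that use, and for these few variables a broader sample is already linked. The conflict between *all* and *mostly* adds to the problem, since a reader cannot tell whether any record from a single profession is in the analysis.

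**Working it through.** **1. The article's own figure.** Linked women divided by participants, both from the Design section: 13,024 / 13,520 = 0.9633, or 96.3%. This reproduces the stated rate. The article gives no sample-size or precision calculation to reproduce.

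**2. Size of the subsample within the linked cohort.** Inputs are 2,884 with hospital records and 13,024 linked.
- Share: 2,884 / 13,024 = 22.1%.
- Remainder: 13,024 − 2,884 = 10,140, or 77.9%.

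This assumes that the 2,884 all lie within the linked cohort and that each counts one mother–neonate pair. The remainder is an upper limit on the usable gain because the article does not say how many linked women have a completed CRF.

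**3. Precision of percent agreement.** Wald 95% half-width = 1.96 × √(p(1 − p)/n). The agreement levels p are assumptions.

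| Assumed agreement | n = 2,884 | n = 13,024 |
|---|---|---|
| 90% | 1.09 points | 0.52 points |
| 95% | 0.80 points | 0.37 points |
| 98% | 0.51 points | 0.24 points |

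The ratio is √(13,024 / 2,884) = 2.13 throughout. A half-width near one point is already narrow for describing agreement, so precision alone would not justify a change.

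**4. What a split by number of professions could show.** The article does not give the number of single-profession records. Assume that 10%, 30% or 50% of the 10,140 are single-profession, and that all other linked records are multi-profession. With 95% agreement in both groups, the half-width of the difference is 1.96 × √(0.95 × 0.05 × (1/n₁ + 1/n₂)).

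| Assumed share | n₁ single | n₂ multiple | Half-width of difference |
|---|---|---|---|
| 10% | 1,014 | 12,010 | 1.40 points |
| 30% | 3,042 | 9,982 | 0.88 points |
| 50% | 5,070 | 7,954 | 0.77 points |

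A descriptive split would thus be informative to within about one and a half points, even at the lowest share assumed.

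**5. Which reading of the sample fits the text.**
- For the restricted reading: the abstract's subsample sentence, the Design section's description of the study as one of a subsample, the statement in the Perined section about the records used, and the comparison within the same mothers and neonates.
- For an open reading: the separate CRF-based dataset named as a denominator, and the column for the number of cases per variable in Table 2. The opening sentence of the data collection section also applies the subsample to Perined and hospital-record data without naming the CRFs.

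The first reading is the more natural one. The second is not excluded.

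**The case against.** The strongest reply is that the article never states the restriction. It names a CRF-based dataset, Table 2 counts cases per variable, and the figure showing the data sources is not available here. This stands: the restriction is inferred, and the figure of 10,140 depends on it. It is also why the denominator should be written down.

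A reader might go further and infer three things that the documents do not support.

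- *That the article calls the restriction to multi-profession records unavoidable.* It does not. The word refers to several professions entering data for referred women, which is a feature of care and not a sampling decision.
- *That the article expects the analysed records to be less accurate, and leaves its question about single and multiple professions untested.* Its conjecture concerns variables, not records. Table 1 will list each variable's source or sources and Table 2 its agreement, so a descriptive comparison between variables is possible, although confounded by type of variable. Comparing single- with multi-profession records is not a stated aim.
- *That the full cohort would isolate the effect of Perined's linkage and decision tree.* It would not. The number of contributing professions goes with referral and pathology. Midwives completed the CRFs with participants and also supply part of the Perined data, so agreement in records from midwives alone could be high because the two sources are not independent.

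It can also be said that precision is already ample, that only a few demographics would gain, and that one common sample for all variables is a defensible choice. The first two points are right. The third would serve as a justification, but the article does not offer it, and it does not fit the claim of a nationally representative low-risk population.

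**Conclusion.** The point holds as a matter of sample choice and clarity. On the most natural reading, CRF-referenced completeness and agreement come from 2,884 at-risk records, 22.1% of the linked cohort, with no reason given, although the reference was collected at enrolment and up to 10,140 more women are linked. The main cost is representativeness: the results would describe a pathology-selected set and not the population that the Discussion claims. The gain in precision, from about 0.80 to 0.37 points at 95% agreement, is secondary and would not by itself change any conclusion.

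This rests on the restricted reading of the sample, on the 2,884 lying within the 13,024, and on CRFs being available for most linked women. It concerns only the CRF demographics; which variables these are cannot be read reliably from the tables as reproduced. Hospital-record variables are unaffected.

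Separately, *all* in the section on Perined data and *mostly* in the Discussion cannot both describe the records analysed. That conflict is certain and does not depend on any assumption.

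**What to change.** 1. State, for each variable, which reference is used and the denominator that goes with it.
2. For CRF-referenced variables, compute completeness and agreement in all linked women with a CRF. Also report the 2,884 subsample, so that these variables can be read beside those referenced to hospital records. If the restriction is kept, give the reason and limit the claim of representativeness accordingly.
3. Where the linked file identifies the contributing professions, report CRF-variable results descriptively for single- and multi-profession records. Note that the contrast is confounded by referral and that midwives supply both the CRF and part of the Perined data.
4. Reconcile the section on Perined data with the Discussion on whether all or most records come from more than one profession.

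The cost is small: a larger extract from data that are already linked, one extra table, and a denominator that differs between CRF and hospital-record variables. No new data collection is needed.

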**Figure 1. f1:**
[figure not shown]
Perined links datasets and creates one record for all neonates and their mothers.
^
24
^

### Data collection and selection

Perined data and extracted hospital record data for the planned comparison study are selected using a subsample of the IRIS study.
Figure 2 shows the used data sources for this study. For the IRIS study hospital records were selected for in-depth data collection based on certain criteria for the Perined or survey data. If the Perined record suggested a case of perinatal death (between 28 weeks pregnancy and 7 days postpartum), a low Apgar score (<4) at five minutes, a birth weight between percentile 2.3 and 5 and neonatal hospitalization for more than three days, or a birth weight < percentile 2.3, data from hospital records were extracted. Hospital records were also selected based on a longitudinal survey; a subsample of women in the IRIS study (n= 1949) took part in this survey.
^
21
^ The survey data were used to identify cases at risk for a severe adverse perinatal outcome. When mothers indicated in the survey that they had a consultation or referral of care to obstetrician-led care, or that their baby visited a paediatrician or neonatologist, they were included for the in-depth data collection from hospital records if they met certain criteria. Maternal indications to be included in the in-depth data collection included maternal hospitalization during pregnancy and/or postpartum or maternal hospitalization for more than 48 hours after birth without medical intervention or an hospitalization of more than 72 hours related to a caesarean section.
^
25
^ Trained research assistants performed the data extraction. After data extraction from the hospital records, the amount of error in data entry was analysed. Double entry analyses were performed on hospital records of 111 women. The incidence of data entry error was 3.2% overall, 3.7% for maternal data and 2.6% for neonatal data.
^
19
^

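### Perined values helped decide which hospital records were extracted, so a pooled kappa for perinatal death, and partly for Apgar <7, is open to partial verification bias

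*Protocol article*

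**What the plan says.** The Data collection and selection section of the protocol article explains that "hospital records were selected for in-depth data collection based on certain criteria for the Perined or survey data". On the Perined side, the rule for death and Apgar reads "If the Perined record suggested a case of perinatal death (between 28 weeks pregnancy and 7 days postpartum), a low Apgar score (<4"; the score meant is the five-minute one. Low birth weight is the other Perined trigger, in two forms: below p2.3, or p2.3–5 when combined with a neonatal stay longer than three days.

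There are two further routes:
- **Survey:** "a subsample of women in the IRIS study (n= 1949) took part in this survey". Women who reported referral or a paediatric visit were included if they met further criteria.
- **Maternal:** "Maternal indications to be included in the in-depth data collection included maternal hospitalization during pregnancy and/or postpartum", together with longer stays after birth. The article does not say for each maternal criterion whether it was read from Perined or from the survey.

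The Design section makes the extracted hospital data a reference standard and gives the number: "Data extracted from the hospital records (n=2884) were collected for neonates at risk for severe adverse perinatal outcomes". It adds that some mothers were included because of such a neonate, or because of their own peripartum problems or a hospital stay.

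Tables 1 and 2 list perinatal death, 5-minute Apgar <7, birth weight, and paediatric consultation or hospitalization among the variables to be compared. Table 2 has one row per variable and no column for selection route. Statistical analyses plans percent agreement, kappa and PABAK for categorical variables and percent agreement and ICC for continuous ones. It attaches strength labels and mentions neither weighting nor separation by route.

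Conclusion and discussion names the transition years and the multi-profession records as weaknesses. It does not mention selection on Perined values, and it gives as the greatest strength that "using a large-scale nationally representative low risk pregnancy population in the Netherlands provides the rare opportunity to validate the quality of Perined data".

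**The concern.** The source under test partly decides who receives the reference standard. For perinatal death and 5-minute Apgar <4, the Perined-positive cases are meant to be checked against the hospital record. A case that Perined missed is checked only if something else about the mother or child brought it in. The cell for Perined no, hospital yes is therefore likely to be thinned out relative to the Perined-positive cells. Kappa for a rare event depends heavily on that cell.

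The article says its results should help researchers choose Perined outcome variables for future studies. Perinatal death and low Apgar are outcomes for which missed cases matter. A pooled kappa with a favourable strength label could hide those misses.

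Separately, the representativeness claim may fit the IRIS cohort, but it does not describe the 2884 records on which the hospital comparisons rest. Those were chosen for at-risk neonates or maternal pathology.

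**Working it through.** **Inputs from the article.** 13,520 participants; 13,024 linked; 2884 hospital records; 1949 survey women.

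**Reproducing the stated figure.** 13,024/13,520 = 96.3%, as the article gives.

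**How much is verified.**
- Extracted overall: 2884/13,024 = 22.1%. Without a hospital reference: 13,024 − 2884 = 10,140 (77.9%).
- Survey share of participants: 1949/13,520 = 14.4%, of whom only those meeting further criteria were extracted.
- Assumption: the birth-weight triggers capture between 2.3% and 5% of linked births, that is 0.023 × 13,024 = 300 to 0.05 × 13,024 = 651 records. Then (2884 − 300)/(13,024 − 300) = 20.3% down to (2884 − 651)/(13,024 − 651) = 18.0% of the remaining births were verified.

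The 22% is an overall extraction fraction. It is not the chance that a case missed by Perined was verified, and the article gives no figure for that chance.

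**Effect on the planned measures for a yes/no event.** The model verifies all Perined-positives and a random share v of Perined-negatives. Assumed: prevalence 1%, Perined sensitivity 60%, specificity 99.95%. Expected counts in 13,024 births:
- both yes: a = 78.1
- Perined yes only: b = 6.4
- hospital yes only: c = 52.1
- both no: d = 12,887.3

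Formulas, with n = a+b+c+d:
- agreement po = (a+d)/n
- chance agreement pe = [(a+b)(a+c) + (c+d)(b+d)]/n²
- kappa = (po − pe)/(1 − pe)
- PABAK = 2·po − 1

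Full verification: po = 0.9955, pe = 0.9836, kappa = 0.0119/0.0164 = 0.725, PABAK = 0.991.

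With v = 18%: c becomes 9.4, d becomes 2319.7 and n = 2413.7. Then po = 0.9934, pe = 0.9312, kappa = 0.0622/0.0688 = 0.905, PABAK = 0.987. About 9 of 52 missed cases are seen.

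| v | kappa | percent agreement | PABAK |
|---|---|---|---|
| full | 0.725 | 99.55 | 0.991 |
| 50% | 0.825 | 99.50 | 0.990 |
| 21.7% | 0.895 | 99.39 | 0.988 |
| 18% | 0.905 | 99.34 | 0.987 |
| 5% | 0.938 | 98.76 | 0.975 |

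Over prevalence 0.3–2%, sensitivity 60–90%, specificity 99.8–99.95% and v 5–50%, kappa exceeded its full-verification value in every case, by 0.01 to 0.22. Percent agreement was lower in every case.

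**If missed cases are verified more often than true negatives.** Keep 18% for true negatives and let a share f of missed cases be verified. Kappa is 0.905 at f = 18%, 0.821 at f = 50%, 0.735 at f = 90% and 0.716 at f = 100%. The inflation shrinks as f rises and is gone when every missed case enters by another route.

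**Birth weight.** In a simulation (mean 3450 g, SD 500 g, 1% gross errors, all assumed) the ICC was 0.990 under full verification and 0.991 with the Perined trigger plus 18% of the rest. It was 0.84 when only the Perined birth-weight route was used, which is not the planned sample.

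**Trigger against compared variable.** The Apgar trigger is <4 and the compared item is <7, so Perined scores of 4 to 6 are not selected on Apgar. A stay of more than three days is a trigger only jointly with birth weight p2.3–5, whereas the compared item is any paediatric consultation or hospitalization.

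**The case against.** The strongest reply is that most of the sample did not come through the Perined triggers. Under the birth-weight assumption above, about 2233 to 2584 of the 2884 records (77% to 90%) entered by other routes. A missed death or very low Apgar score may well coincide with maternal hospitalization or a reported paediatric visit, so f could be far above 18%. This stands: the size of the bias is unknown, and the last calculation shows that it could be small. But the article gives no figure that would settle it, and route-separated reporting is what would.

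Several stronger readings are tempting and should not be drawn:
- **All agreement measures are flattered.** Under random verification kappa rises, but percent agreement and PABAK are about equal or lower.
- **A true sensitivity of 70% would appear as 91%.** This takes 22% as the chance that a missed case was verified, which the article does not support. Sensitivity is also not among the planned measures.
- **Selection moves the birth-weight ICC from good to excellent.** This needs assumed error and spread values; with many records from other routes, the ICC barely moves.
- **Neonatal consultation or hospitalization is affected in the same way as death.** It is touched only indirectly.

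It is also fair to say that the article openly describes an at-risk subsample, and that the representativeness phrase can be read as describing the IRIS cohort. That makes it loose wording, but it is offered as the greatest strength of the validation and needs a qualifier. Extraction was done for the parent trial and cannot be repeated, so the remedy is confined to analysis and reporting.

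**Conclusion.** The concern holds in a limited form. Extraction of the reference standard depended partly on the Perined values of items that are then tested, and the article plans one pooled, unweighted figure per item without naming this as a limitation. The problem is clearest for perinatal death. It is partial for Apgar <7, through the <4 component only. It is probably small for the birth-weight ICC and indirect for paediatric consultation or hospitalization.

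The expected direction is a kappa that is too high. In the illustrated case 0.725 becomes 0.905, which moves the article's own label from substantial to almost perfect. Prevalence, sensitivity, specificity and the verified shares are all assumptions, as is the premise that every Perined-positive record was extracted. The inflation vanishes if nearly all missed cases entered by other routes. The documents do not support a single figure for the bias, nor a claim that Perined's missed cases went entirely unseen.

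**What to change.** 1. Derive the selection route for each record (Perined criterion, survey, maternal indication). If no flag survives in the anonymised file, rebuild the Perined route from the Perined criteria values. Report the number of records per route.
2. For perinatal death and Apgar, and for birth weight as a check, report two results: (a) the confirmation rate among records selected on the Perined value, and (b) agreement and the number of missed cases among records selected independently of that value. Weighting by selection probability is an alternative to (b) if those probabilities can be estimated. Do not attach a strength label to a pooled kappa alone.
3. In Conclusion and discussion, state the verification limitation. For the hospital-record comparisons, replace the nationally representative low-risk description with one of the at-risk, hospital-involved subsample.

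No new data collection is needed. The cost is some work to reconstruct the route, which may be incomplete where the source of a maternal criterion is not recorded. Events among independently selected records will be few, so intervals will be wide, particularly for perinatal death, and the overall claim becomes narrower.
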